# Statistical Procedures

## Definition of Study Population to be Analyzed

The primary analysis population will be the intention-to-treat (ITT) population consisting of all randomized subjects, where each subject will be analyzed within the randomized group regardless of the actual treatment.

## Analysis Variables

The primary and secondary endpoints as defined in section 2.1 and 2.2 will be analyzed.

Baseline is defined as last assessment before randomization.

## General Considerations

Further analyses will be defined in the statistical analysis plan (SAP) which has to be authorized before analysis commences by the biometrician and the sponsor. All below mentioned analyses will be described in greater detail in the SAP.

The primary analysis will be conducted when all subjects completed visit 3 of the trial. An additional analysis will take place when all subjects completed the follow up.

SAS version 9.4 or higher will be used for analyses.

## Primary Analysis

**Efficacy analysis:** In the primary analysis, the time to relapse as defined in section 2.1 will be analyzed with a mixed cox regression model with planned treatment, strata (clozapine taken Yes/No, see section 3.4.1) and BPRS at baseline as fixed effects and site as random effect in all subjects randomized (ITT). Subjects with missing information (including death) will be considered as relapses at the time point of last information. The occurrence of other intercurrent events is considered irrelevant in defining relapse (treatment policy strategy). Patients without relapse until visit 3 will be censored at visit 3 (due to possible change of intervention). The middle time point between date of awareness and the prior visit will be used to calculate the time to relapse.

The treatment effect will be tested using a two-sided alpha of 0.05 and in addition, a 95%-confidence interval will be calculated.

## Secondary Analyses

The number of relapse free subjects at the end of phase II will be analyzed by a mixed logistic regression model (two-sided alpha=0.05) with planned treatment, strata and BPRS at baseline as fixed effects and site as random effect in all subjects randomized (ITT).

BPRS, GAF, PANSS, HAMD, NCRS-dv, Q-LES-Q-18, SSMIS-SF and stigma-stress-scale will be categorized considering relapses and dropouts as additional categories. These will be tabulated using standard descriptive measures including number of non-missing values, mean, standard deviation, extrema and quartiles.

Furthermore, to analyze BPRS, GAF, PANSS, HAMD, NCRS-dv, Q-LES-Q-18, SSMIS-SF and stigma-stress-scale per time-point linear mixed models with the respective scale at baseline, strata and treatment as fixed effects and site as random effect will be used.

An explorative analysis will be carried out for all recruited subjects, where a logistic regression will be performed for the rate of inclusion in the randomized trial on baseline criteria. This way, subjects likely to profit from a first session of ECT can be determined based on clinical criteria.

**Safety analysis:** Frequencies of subjects experiencing at least one adverse event (AE) will be displayed according to MedDRA terminology. MMSE and THINC-it will be analyzed by group using standard descriptive measures.

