| Mini Mental State^6^ Examination |  | **x** | **x** | **x** | **x** | **x** | **x** | **x** | **x** | **x** | **x** | **x** |
| THINC-it ®^6^ |  | **x** | **x** | **x** | **x** | **x** | **x** | **x** | **x** | **x** | **x** | **x** |
| Northoff Catatonia Rating Scale (German version) |  | **x** | **x** |  |  |  |  |  | **x** | **x** | **x** | **x** |
| Q-LES-Q-18 |  | **x** | **x** |  |  |  |  |  | **x** | **x** | **x** | **x** |
| Self-Stigma of Mental Illness Scale – Short Form |  | **x** | **x** |  |  |  |  |  | **x** | **x** | **x** | **x** |
| Stigma-Stress-Scale |  | **x** | **x** |  |  |  |  |  | **x** | **x** | **x** | **x** |

ECT: Electroconvulsive Therapy; mECT: Maintenance Electroconvulsive Therapy; TAU: treatment as usual; THINC-it: THINC integrative tool; Q-LES-Q-18: Abbreviated Quality of Life Enjoyment and Satisfaction Questionnaire

*Stabilization: implementation of any major medication changes before the initiation of the ECT series

** The times indicated as weeks refer to the TAU group, however the respective mECT should be scheduled within the respective week. Visit 2 is regarded to take place in week 0, e.g. calendar week 20. For the patients receiving mECT, the first mECT should be scheduled in the next calendar week, e.g. calendar week 21, and the 3^rd^ mECT (Visit 2a) should take place in calendar week 3 after V2, e.g. calendar week 23. A calendar week is from Monday to Sunday. Two mECTs cannot be performed in the same calendar week

^1^ Sociodemographics: Age, sex, education, marital status, residence

^2^ Vital signs: height, weight

^3^ All baseline characteristics (including vital signs, medical history, prior medication, …) must be assessed **before** randomization. Randomization should be carried out only in subjects with improvement of 30% or more on the Brief Psychiatric Rating Scale (BPRS).

^4^ According to randomization

^5^ Treatment depending on patients’ choice

^6^ Mini-Mental State Examination (MMSE) and Thinc-it must be performed before mECT is administered.

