# Study Design

This is a German multi-center, observer-blind, randomized, and actively controlled parallel-group study to compare after a successful series of routine electroconvulsive therapy (ECT) the overall effectiveness of maintenance ECT (mECT) plus treatment as usual (TAU) versus TAU only in subjects aged from 18 to 65 years with the indication of clozapine resistant schizophrenia.

A schematic of the study design is shown below:

[figure not shown]

**Phase I:** Subjects will be included in the study according to the inclusion and exclusion criteria and will receive an ECT series with a maximum of 18 ECT treatments based on a clinical indication for ECT or until there is a clinically sufficient response to treatment.

**Phase II:** Subjects who respond to ECT in phase I (BPRS score < 70% of BPRS at visit 1) meet the inclusion criteria for phase II of the study. After completing the ECT series in phase I and before starting phase II, subjects are randomized to receive either maintenance ECT plus standard treatment or standard treatment alone.

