## Sample Size / Power Calculation

Relapse rates after 6 months of treatment in phase II are estimated to be 90% in the TAU arm and 40% in the mECT + TAU arm based on a clinical trial with a similar study design, a systematic review and a recent open label CRS mECT study (24, 25, 42). In this calculation, more conservative relapse rates of 85% (TAU) and 45% (mECT + TAU) are assumed; although most evidence indicates even lower relapse rates for mECT + TAU, but our subjects might be more severely affected drug resistant subjects. We are aiming for sufficient power for the composite endpoint strategy where missing values are treated as relapses, which increases the relapse rates. With expected rates of missing values of 15% (TAU) and 30% (mECT + TAU) due to higher inconvenience with mECT +TAU, the relapse rates for planning the sample size are 87.25% (TAU) and 61.5% (mECT + TAU). This yields hazard rates of 0.3433 and 0.1591 and a hazard ratio of 0.4634, which in this case is a conservative approach.

Including 84 subjects (42 per group) in phase II, a difference could be found with a power of 0.85 using a cox regression with alpha= 0.05 (two-sided) and considering the reduced effect due to missing values as specified above. Even if the expected hazard rate in the MECT+TAU arm is 0.17 (≙ 63.9%) e.g. due to lower effects or due to a bias because of different observation schedules, the power is still ~80%. (The necessary sample size was simulated using R.) 140 subjects must be enrolled in phase I, if 60% of subjects are responders and willing to participate in phase II of the trial.

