**Compliance / Rate of loss to follow up**

140 subjects must be enrolled, if 60% of subjects are willing to participate in phase II of the trial. We then expect withdrawal rates in phase II of 15% (TAU) and 30% (mECT + TAU) due to higher inconvenience with mECT.

Data Management

For more details refer to the corresponding data management plan (DMP). All data management activities will be conducted according to the current SOPs.

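### The exploratory model for who benefits from acute ECT uses randomization as its outcome, which mixes response with willingness to continue

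*Protocol*

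**What the plan says.** Section 9.5 (Secondary Analyses) gives the population, the outcome and the interpretation of this analysis. On the population: "An explorative analysis will be carried out for all recruited subjects". On the outcome: "a logistic regression will be performed for the rate of inclusion in the randomized trial on baseline criteria". On what it will show: "This way, subjects likely to profit from a first session of ECT can be determined based on clinical criteria".

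Three places in the protocol describe what takes a subject from phase I into the randomized phase, and they differ:

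- Section 9.9 derives the enrolment of 140 on the condition "if 60% of subjects are responders and willing to participate in phase II of the trial", that is, response and willingness together.
- The paragraph on compliance and loss to follow-up directly after it names willingness only: "140 subjects must be enrolled, if 60% of subjects are willing to participate in phase II of the trial".
- The synopsis (Interventions) says that every ECT responder goes on into phase II, which would make inclusion the same thing as response.

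Response is defined from the BPRS. Section 3 has "Subjects who respond to ECT in phase I (BPRS score < 70% of BPRS at visit 1) meet the inclusion criteria for phase II". The synopsis, footnote 3 of the schedule of assessment and section 6 instead require an improvement of at least 30%. The schedule places the BPRS at visit 1 (before the first ECT) and at visit 2 (one day after the last ECT of the series).

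**The concern.** The stated aim is to learn which patients benefit from the acute ECT course. The modelled outcome is whether a patient was randomized. By section 9.9 that requires two things, and only one of them is benefit. The not-included group can therefore hold patients who did not respond, patients who responded but did not go on, and patients who left before visit 2. The interpretation in section 9.5 treats them all as not profiting.

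Two errors can follow. A baseline characteristic that affects only willingness to continue can look like a predictor of ECT benefit. A real predictor of response can look weaker than it is. Neither is necessary, because the sites must determine response anyway before they may randomize.

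**Working it through.** **Inputs.** 140 subjects enrolled and 84 randomized (section 4.1); a joint rate of 60% (section 9.9). The response rate *r* and the willingness rate among responders *w* are not given separately. Only their product is: *r* × *w* = 0.60.

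**The plan's own figure.** 84 / 0.60 = 140, which reproduces the stated enrolment exactly. The planning figure thus rests on the joint rate.

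**Responders in the not-included group.** The group has 140 − 84 = 56 subjects. The responders among them number 140*r* − 84. The values of *r* below are assumptions.

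| Assumed *r* | Responders, 140*r* | Implied *w* = 0.60/*r* | Responders not randomized | Share of the 56 |
|---|---|---|---|---|
| 60% | 84 | 100% | 0 | 0% |
| 65% | 91 | 92.3% | 7 | 12.5% |
| 70% | 98 | 85.7% | 14 | 25% |
| 80% | 112 | 75% | 28 | 50% |

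Inclusion and response coincide only in the first row, where every responder is randomized.

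**What this could do to an odds ratio (illustration, all inputs assumed).** Take a binary baseline predictor present in half of the subjects.

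- *Real predictor, willingness unrelated to it.* Let the odds ratio for response be 3. At *r* = 70% the response rates are 0.589 and 0.811. Multiplying by *w* = 0.857 gives inclusion rates of 0.505 and 0.695, and an odds ratio for inclusion of 2.24. At *r* = 80% the response rates are 0.717 and 0.883, *w* = 0.75, and the odds ratio for inclusion is 1.69.
- *No effect on response, willingness 10 points above or below its mean.* At *r* = 70% the inclusion rates are 0.70 × 0.757 = 0.53 and 0.70 × 0.957 = 0.67, an odds ratio of 1.80. At *r* = 80% they are 0.80 × 0.65 = 0.52 and 0.80 × 0.85 = 0.68, an odds ratio of 1.96.

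The proxy can therefore both dilute a true association and create a false one. The documents do not show how far either would happen here.

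**The case against.** The best defence is that inclusion tracks response closely in this design. The synopsis sends all responders into phase II, consent is scheduled once at screening, and no second consent before randomization is described. A responder would then be missed mainly by withdrawing. This lowers the likely number but does not remove the mismatch: the enrolment of 140 is built on response and willingness jointly, and section 7 lets any subject withdraw at any time, including before randomization.

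Inclusion also has a practical merit. It is known for every recruited subject and counts phase I dropouts as unsuccessful without a further rule. That stands, and the fix has to deal with it.

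Section 9.3 leaves detail to the SAP. But section 9.5 already states the outcome and the conclusion drawn from it, so the point concerns what is written and not something left out.

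Three stronger readings are tempting, and the documents do not support them:

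- *That decliners are coded as non-responders.* No such code exists. They are coded as not included, and only the interpretive sentence treats them as not profiting.
- *That a sizeable share of the 56 is misread.* The number could be 0, and nothing in the protocol supports any particular response rate above 60%.
- *That the trial's main conclusions are at risk.* The analysis is labelled exploratory and serves no objective or endpoint listed in section 2.

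**Conclusion.** The point holds as a mismatch between outcome and interpretation. A model of inclusion estimates who responds and also goes on to randomization; it cannot by itself identify who profits from acute ECT. The size is not derivable from the protocol: between 0 and 28 of the 56 subjects not included, for response rates assumed between 60% and 80%. The odds ratios above show the direction of possible error under assumed inputs and are not estimates for this trial.

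The primary analysis, its alpha, the 84 randomized subjects and the power are unaffected. The correction is still worth making, because a direct measure of response is already scheduled and this is the only analysis in section 9 that uses all phase I subjects.

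**What to change.** In section 9.5, replace the outcome by BPRS response at visit 2 under the protocol's own criterion (improvement of at least 30% from visit 1), for all recruited subjects. State a rule for subjects without a visit 2 BPRS, for example counting them as non-response, with a complete-case analysis as a check. Report how many responders were not randomized. If the sponsor prefers to keep inclusion as the outcome, the interpretive sentence should say instead that the model predicts entry into phase II.

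Three pieces of wording should be settled at the same time:

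- The synopsis, section 9.9 and the compliance paragraph should agree on whether the 60% is response, willingness or both.
- Section 3 and the other places should agree on the response criterion, since a subject at exactly 70% of the visit 1 score is a responder under one version and not under the other.
- The reference in section 9.5 to a first session should match the assessment at visit 2, which follows the whole ECT series. This is a matter of wording only.

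The cost is small: a few sentences and no new assessments. There are two downsides. A missing-data rule is needed for phase I dropouts. If response exceeds 60%, the smaller outcome class also shrinks from 56 to 140 − 98 = 42 at 70% or 140 − 112 = 28 at 80%, which limits how many predictors the model can carry.

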# PROTOCOL SYNOPSIS

| **Full Title** | Maintenance ElectroConvulsive Therapy in clozapine RESISTant schizophrenia |
| --- | --- |
| **Study Code** | MECT-RESIST |
| **Rationale** | Schizophrenia is one of the most severe and costly mental disorders in terms of human suffering and societal expenditure. About 15-30% of patients do not respond to all known antipsychotics, including clozapine, the current gold-standard in these cases. Electroconvulsive therapy (ECT) is well known to be highly effective in clozapine-treatment-resistant schizophrenia (CRS), and synergistic effects of clozapine and ECT have been demonstrated. However, relapse rates after successful courses of ECT are still very high, and evidence for maintenance ECT (mECT) in CRS is scarce at best. In our multi-center trial, we aim to examine the effectiveness of mECT in treatment-resistant patients with schizophrenia who improved after a course of routine ECT.  The scientific aim of the study is to test the hypothesis that maintenance ECT (mECT) plus treatment as usual (TAU) (intervention group) is superior to TAU alone (control group) for relapse prevention in CRS. The effectiveness of mECT will be examined by comparing time to relapse in the intervention group with the control group expecting a longer time to relapse in the intervention group. Secondarily, a lower number of patients with relapse is expected in the intervention group compared to the control group. Further secondary objectives are to test the hypotheses that the global level of functioning and quality of life will increase, and that depression, overall symptoms of the schizophrenic syndrome, concomitant catatonic symptoms, stress and self-stigmatization will decrease compared to the control group. It is also hypothesized that cognitive performance will improve over the course of the mECT. |

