| **Primary Objective and Endpoint** | To compare after a successful series of routine electroconvulsive therapy (ECT) the overall effectiveness (time to relapse) of maintenance ECT (mECT) plus treatment as usual (TAU) versus TAU only.  Endpoint: Time to relapse (relapse defined as Brief Psychiatric Rating Scale (BPRS) ≥20% higher than individual BPRS at start of phase II at any following study visit OR any unscheduled readmission due to a worsening of psychiatric symptoms OR any unscheduled visit with an BPRS ≥20% higher than individual BPRS at start of phase II). The BPRS is evaluated by an unblinded rater at site and a blinded central rater. Readmission is decided by unblinded non-study related staff. The first relapse decision is used for analysis. |
| **Main Secondary Objectives and Endpoints** | 1. To compare side effect profile and safety between mECT plus TAU and TAU only 2. To compare psychopathological changes: mECT plus TAU versus TAU only   Endpoints:  - Number of relapse free subjects at the end of phase II  - BPRS at the end of phase II  - GAF, PANSS, HAMD, NCRS-dv, Q-LES-Q-18, SSMIS-SF, stigma-stress-scale at the end of phase II  - BPRS, GAF, PANSS, HAMD, NCRS-dv, Q-LES-Q-18,  SSMIS-SF, stigma-stress-scale at the end of follow-up  Assessment of safety:  Cognitive side effects profile (MMSE, THINC-integrated tool [THINC-it])  and safety. |
| **Study Design** | This is a multi-center, observer-blind, randomized, and actively controlled parallel-group clinical trial. |
| **Sample Size** | To be assessed for eligibility (n = 300)  To be allocated to trial (n = 140 in phase I)  To be analyzed (n = 84 randomized in phase II) |
| **Study Population** | Subjects (aged 18-65 years) with current diagnosis of schizophrenia according to Diagnostic and Statistical Manual of Mental Disorders, Fifth Edition (DSM-5), BPRS total score > 45 and history of clozapine resistant schizophrenia (CRS), which will include treatment-resistant schizophrenia with clozapine intolerance or absolute contraindications for clozapine. |

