# SCHEDULE OF ASSESSMENT

| **Phase (duration)** | **0** | **I** | | **II** | | | | | | **Follow-Up** | | **Unscheduled**  **Visit** |
| --- | --- | --- | --- | --- | --- | --- | --- | --- | --- | --- | --- | --- |
|  | max. 1 week | Initial ECT series  (max. 6 weeks and max. 18 ECTs are allowed) | | 28 weeks | | | | | | 12 months | |  |
| **Visit** | **Screening/ inclusion** | **1** | **2** | **2a** | **2b** | **2c** | **2d** | **2e** | **3** | **4a** | **4b** |  |
| **Time** | Before start of stabilization*  (max. 7 days before visit 1) | 1-2 day(s) before the first ECT | 1 day after last ECT (week 0) | 3rd calendar week ** or  on the day of the 3rd mECT | 6^th^ calendar week after V2 or  on the day of the 6th mECT | 10^th^ calendar week after V2 or on the day of the 8th mECT | 14^th^ calendar week after V2 or on the day of the 10th mECT | 19^th^ calendar week after V2 or on the day of the 12th mECT | 28^th^ calendar week after V2  or on the day of the last mECT | 6 mo. after visit 3 | 12 mo. after visit 3 |  |
| Informed Consent | **x** |  |  |  |  |  |  |  |  |  |  |  |
| In-/Exclusion Criteria | **x** |  |  |  |  |  |  |  |  |  |  |  |
| Sociodemographics^1^ |  | **x** |  |  |  |  |  |  |  |  |  |  |
| Medical History |  | **x** |  |  |  |  |  |  |  |  |  |  |
| Concomitant Medication / Therapy |  | **x** | **x** | **x** | **x** | **x** | **x** | **x** | **x** | **x** | **x** | **x** |
| Vital Signs^2^ |  | **x** |  |  |  |  |  |  | **x** |  | **x** | **x** |
| Randomization^3^ |  |  | **x** |  |  |  |  |  |  |  |  |  |
| Adverse events |  |  |  | **x** | **x** | **x** | **x** | **x** | **x** | **x** | **x** | **x** |
| **Intervention** |  |  |  |  |  |  |  |  |  |  |  |  |
| TAU or mECT + TAU |  |  |  | **x**^4^ | **x**^4^ | **x**^4^ | **x**^4^ | **x**^4^ | **x**^4^ | **x**^5^ | **x**^5^ |  |
| **Questionnaires/tests** |  |  |  |  |  |  |  |  |  |  |  |  |
| Brief Psychiatric Rating Scale |  | **x** | **x** | **x** | **x** | **x** | **x** | **x** | **X** | **x** | **x** | **x** |
| Global Assessment of Functioning |  | **x** | **x** | **x** | **x** | **x** | **x** | **x** | **x** | **x** | **x** | **x** |
| Positive and Negative Symptom Scale |  | **x** | **x** | **x** | **x** | **x** | **x** | **x** | **x** | **x** | **x** | **x** |
| Hamilton Rating Scale for Depression |  | **x** | **x** | **x** | **x** | **x** | **x** | **x** | **x** | **x** | **x** | **x** |

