## Risk Benefit Assessment

All procedures performed during this study are routine clinical procedures and are mentioned within German guidelines. Of course, all side effects will be recorded. Severe side effects are not expected (27), since they are known to be extremely rare (and not study related).

The most common side effect in phase one will be cognitive side effects due to ECT. These will be monitored not only by MMSE, but also by THINC-it and by clinical observation. THINC-it has been validated multiple times in the past (28), especially for treatment-related changes of cognitive function in both depression (29) and schizophrenia (30). Of course, this monitoring will continue in phase two as well, although significant differences between groups are not expected to occur during this phase. Typically, cognitive side effects after an acute ECT series subside after about 15 days (31). There is no evidence for further decline of cognitive function with maintenance ECT (32), but evidence of further improvement.

Participants might personally benefit from study participation due to closer and more standardized monitoring compared to routine clinical practice. Future patients with clozapine-resistant schizophrenia will benefit from the study results, as they will most likely lead to a change in guidelines for treatment-resistant schizophrenia.

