**Phase I**

- Study visits 1 and 2 with psychometric assessments
- Full course of routine ECT (max. 18 sessions; 3x/week)
- Randomization (at the end of visit 2) of subjects with improvement of 30% or more on the Brief Psychiatric Rating Scale (BPRS)

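### MMSE and THINC-it have no planned between-arm estimate, and a rise from visit 2 within the mECT arm can be misread as supporting the cognitive hypothesis

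*Protocol*

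**What the plan says.** Five parts of the protocol bear on this.

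- **Objective.** The synopsis gives as its first main secondary objective: "To compare side effect profile and safety between mECT plus TAU and TAU only". Section 2.2 repeats the comparative aim and lists MMSE and THINC-it among the secondary endpoints, to be analysed when phase II ends and again when follow-up ends.
- **Hypothesis.** The synopsis rationale adds: "It is also hypothesized that cognitive performance will improve over the course of the mECT". That sentence names no comparator.
- **Analysis.** Section 9.5, under safety, says: "MMSE and THINC-it will be analyzed by group using standard descriptive measures". For BPRS, GAF, PANSS, HAMD, NCRS-dv, Q-LES-Q-18, SSMIS-SF and the stigma-stress scale, the same section plans "linear mixed models with the respective scale at baseline, strata and treatment as fixed effects", with site as a random effect.
- **Baseline.** Section 9.2: "Baseline is defined as last assessment before randomization". Section 6 places randomization at the close of visit 2, and the Schedule of Assessment times that visit as "1 day after last ECT (week 0".
- **Recovery.** Section 1.3: "Typically, cognitive side effects after an acute ECT series subside after about 15 days (31".

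Both tests are scheduled in both arms at visit 1 (before the first ECT), at visit 2, and at all six phase II visits. On mECT days they are done before the treatment.

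**The concern.** A comparative objective has been paired with an analysis that yields no planned comparison. Section 9.5 chooses this explicitly: it names eight scales for modelling and assigns the two cognitive tests to description.

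The timing of visit 2 makes this matter more than usual. All randomized patients have just finished an acute ECT series, so their visit 2 scores can be expected to sit below their recovered level. The hypothesis speaks of improvement over the course of mECT and names no control, so a rise within the mECT arm could be reported as confirming it although it reflects only recovery from phase I. At stake are a cognitive benefit claimed for mECT without support, and a safety question left without an interval showing what size of cognitive cost can be excluded.

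**Working it through.** **The protocol's own figures.** The protocol gives no power or precision for cognition. Its only such figure, for the primary endpoint (section 9.9), reproduces:

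- Composite relapse rates: 0.85 + 0.15 × 0.15 = 0.8725 (TAU) and 0.45 + 0.55 × 0.30 = 0.615 (mECT + TAU).
- Hazards −ln(1 − p)/6 = 0.3433 and 0.1591, giving a hazard ratio of 0.4634.
- Expected events 42 × (0.8725 + 0.615) = 62.5. Power by the Schoenfeld formula is 0.86, against 0.85 stated.

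**Timing.** Visit 2 is day 1 after the last acute ECT. Visit 2a is in calendar week 3 after visit 2, nominally 3 × 7 = 21 days later. Under the Monday-to-Sunday rule, the shortest gap (Sunday of week 0 to Monday of week 3) is 1 + 14 = 15 days after visit 2, or 16 days after the last ECT. The stated recovery of about 15 days therefore falls between baseline and the first follow-up test, in both arms.

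**Size of the within-arm artefact.** Suppose mECT has no effect and both arms start with an acute deficit D at visit 2 that has resolved by the next test. The documents give neither D nor the correlation ρ between baseline and follow-up, so both are assumed: D from 0.2 to 0.8 SD, ρ of 0.5 or 0.7. The expected gain in the mECT arm equals D. Its standard error with n = 42 is √(2(1 − ρ)/42), which is 0.154 SD at ρ = 0.5 and 0.120 SD at ρ = 0.7. Results of 20,000 simulated trials per setting:

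| D (SD) | Nominally significant gain within mECT arm | Mean mECT − TAU difference in change | Nominally significant between arms |
|---|---|---|---|
| 0.2 | 24% to 37% | 0.00 | about 5% |
| 0.4 | 72% to 90% | 0.00 | about 5% |
| 0.6 | 97% to 100% | 0.00 | about 5% |
| 0.8 | 100% | 0.00 | about 5% |

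The artefact arises only in the within-arm reading and cancels in the comparison with TAU.

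**Precision of the missing estimate.** For a baseline-adjusted difference, the standard error is √((1 − ρ²)(1/n₁ + 1/n₂)) in SD units, with ρ assumed from 0.7 down to 0.

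| Patients tested (TAU, mECT) | 95% CI half-width | Detectable with 80% power |
|---|---|---|
| 42, 42 | 0.31 to 0.43 SD | 0.44 to 0.61 SD |
| 42 × 0.85 = 35.7, 42 × 0.70 = 29.4 (stated withdrawal) | 0.35 to 0.49 SD | 0.50 to 0.70 SD |
| 42 × 0.1275 = 5.4, 42 × 0.385 = 16.2 (only relapse-free patients) | 0.70 to 0.98 SD | 1.0 to 1.4 SD |

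The last row is a worst case at visit 3. It applies only if patients who relapse or withdraw have no cognitive test then. Section 6 asks for visit 3 assessments when participation ends early, so actual numbers should be higher, though those tests may come before week 28.

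**The case against.** The strongest reply is that the control arm already handles the problem. TAU patients have the same acute series behind them and are tested at the same visits, so a by-group table would show them recovering too. If mECT slowed recovery, its column would lag. This stands: a reader might infer that the tables will show a false improvement under mECT, but that requires ignoring the TAU column. It is a risk created by the comparator-free hypothesis, not a certain result.

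Other parts of the reply also stand.

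- Section 9.5 does not say that cognition is tabulated as change from baseline. The reference to visit 2 comes from the general definition in section 9.2.
- Visit 1 supplies a score from before the ECT series, so a by-visit table could show the acute dip and the recovery.
- Section 2.2 directs the analysis to the end of phase II and of follow-up. By week 28, recovery from the acute series should be complete in both arms, so a slower early recovery is a question for visit 2a, not visit 3.
- A reader might infer that the trial could not say whether mECT costs cognition. Group means and SDs would still give a crude randomized difference.
- A reader might also take cognition to be the main harm expected of mECT. Section 1.3 calls cognitive effects the most common side effect in phase one and expects no significant group difference in phase II.

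The appeal to the SAP is weaker. Section 9.3 lets the SAP add analyses, but section 9.5 has already assigned these two endpoints to description. Nor is a crude difference equivalent to the modelled one. With 42 per arm, the chance imbalance at visit 2 has a standard error of √(2/42) = 0.22 SD, which unadjusted means do not correct. An expectation of no group difference is also only informative with an interval around the observed one.

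**Conclusion.** The point holds as a mismatch between objective and analysis. Two secondary endpoints that serve a comparative safety objective have no planned adjusted treatment difference or interval, although the model used for eight other scales would provide both. In addition, within-arm change from visit 2 cannot support the synopsis hypothesis, because the protocol's own 15-day figure predicts a rise in both arms without any mECT effect.

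The size of that rise is unknown. At an assumed deficit of 0.4 SD it would be nominally significant within the mECT arm in 72% to 90% of trials. This rests on 42 patients tested, a deficit fully resolved by the next test, and a correlation of 0.5 to 0.7. The documents do not support the claim that the planned tables must mislead or that no comparison would be possible. The primary analysis is unaffected. The protocol should be changed, since the change costs little and uses data already scheduled.

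**What to change.** 1. In section 9.5, add MMSE and THINC-it to the scales analysed by linear mixed model, with visit 2 score, strata and treatment as fixed effects and site as random effect. Report the mECT-minus-TAU difference with its 95% CI at each phase II visit, chiefly visit 3, which section 2.2 requires.
2. Tabulate visit 1 scores alongside, and the number contributing per arm at each visit. Relapse and the unequal withdrawal expected (15% TAU, 30% mECT + TAU) select who is tested, and the model does not remove that selection.
3. Reword the synopsis hypothesis as a between-arm comparison, and state that within-arm change from visit 2 is not evidence of an mECT effect.
4. Name the THINC-it score to be modelled, since section 6.2 describes four objective tests and a subjective questionnaire. Note that the MMSE maximum of 30 limits a linear model.

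The cost is protocol and SAP wording and a small amount of added analysis, with no new data or visits. The intervals will be fairly wide (half-width about 0.3 to 0.5 SD, wider if few patients are tested at visit 3), so a modest cognitive cost may remain unresolved.
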